### Conceptual framework

Empirical evidence on mechanisms by which environmental factors influence physical activity is largely lacking [54]. Therefore, we drew on socio-ecological frameworks and observational studies to conceptualise how physical and social environmental factors may influence walking behaviour among older adults. Our conceptual framework is depicted in Fig. 2, and suggests a direct influence of the environment on walking behaviour [55] and two indirect mechanisms:Mediation by perceived environmental and cognitive factors: Environments conducive to walking are hypothesized to positively influence perceptions of the walking environment [42, 55], which may positively influence motivational determinants of walking (Fig. 2), such as attitudes towards walking.Moderation of the relation between the intention to walk and walking behaviour. Social and physical environmental factors may facilitate transferring intentions to behaviour [56–58]. In other words, environmental changes may help to mitigate the intention-behaviour gap (i.e. no behaviour change despite having a positive intention towards the new behaviour) which was found for different lifestyle behaviours [59], including physical activity [60, 61]. Thus, for older adults with positive intentions to walk, modifying the physical and social environment may facilitate them to act accordingly (Fig. 2).

**Fig. 2 Fig2:**
[figure not shown]
Conceptual framework of the NEW.ROADS study

### Measurements

For the overall evaluation of the interventions in terms of walking behaviour, and to understand the underlying mechanisms, participants receive a questionnaire pack at each time point. Table 1 schematically shows which constructs will be measured at each time point.

**Table 1 Tab1:** Timeline of measurements during the effect and process evaluation of the NEW.ROADS study

	*T0*	*T1*	*T2*
Time	February/March	August/September	November/December
Primary outcomes	*Self reported walking (IPAQ)*	*Self reported walking (IPAQ)*	*Self reported walking (IPAQ)*
Secondary outcomes	*MVPA (IPAQ)* *Perceived health (SF12)*	*MVPA (IPAQ)*	*MVPA (IPAQ)* *Perceived health (SF12)*
Determinants	*Perceived environmental factors (NEWS)* *Social cohesion and social capital* *Theory of Planned Behaviour constructs*	*Perceived environmental factors (NEWS)* *Social cohesion and social capital* *Theory of Planned Behaviour constructs*	*Perceived environmental factors (NEWS)* *Social cohesion and social capital* *Theory of Planned Behaviour constructs*
Process evaluation	*GPS*	*GPS* *Walk along interviews*	*GPS* *Questionnaire: awareness, use and appreciation* *Phone interviews*

#### Outcomes

Self-reported physical activity will be measured by means of the IPAQ long version [62]. The primary outcome measure will be weekly minutes spend walking in leisure time and for transport. Secondary outcome measures include moderate-to-vigorous physical activity (IPAQ), objectively measured levels of MVPA (measured with accelerometers) and perceived health [63].

#### Understanding the underlying mechanisms: mediating factors

To study the proposed mechanisms, we will measure neighbourhood perceptions, using the Neighbourhood Environment Walkability Scale (NEWS) [64], Theory of Planned Behaviour constructs [65] and social cohesion and social capital constructs in questionnaires.

#### Understanding the intervention effect: process evaluation

The process evaluation of NEW.ROADS will consist of various components with the aim to understand the awareness, use acceptability, feasibility, implementation and appreciation of the interventions among participants. This will be done by using a number of activities ranging from the analysis of GPS tracks and accelerometer data, to conducting walk-along interviews, and analysis of questionnaire data.

Whether people use the walking routes will be measured in a 10 % subsample of older adults, by means of GPS loggers (Travel recorder X, BT-Q1000X, QStarz International). The BT-QStarz GPS logger has a relatively good performance in terms of accuracy and battery life. The participants will be instructed to charge the GPS logger overnight, while keeping it switched on – previous studies have shown high compliance with this procedure (Jones et al., [66]).

To get insight in the perceptions of the participants on the walking route, walk-along interviews will be held with 30 participants from neighbourhoods in the physical environment condition. During these walk along interviews, the participants walk a part of the walking route with members of the research team. The walk will be recorded with two voice recorders (one for the member of the research team and one for the participant) and a GPS logger. Moreover, geo-coded photographs will be taken from important physical or social environmental characteristics.

In the final questionnaire at T2, items about awareness, use and appreciation of the environmental changes from the participant’s point of view will be measured. To get further insight in this, a random selection of 100 participants will be phoned and asked about their awareness of the route and ways to further improve the route.

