### Evaluation design, participants and recruitment

The environmental interventions are evaluated in a four-armed experimental study on changes in minutes walked. These four arms correspond to four neighbourhoods, namely: 1) a neighbourhood with the physical environmental intervention, 2) a neighbourhood with the social environmental intervention, 3) a neighbourhood with both physical and social environmental interventions and 4) a control neighbourhood (no interventions). These neighbourhoods were selected in close collaboration with policy makers on their comparability (demographics, physical environment). Although random allocation to study arms was envisaged, due to collaboration with ongoing activities assignment to the study arms was mostly based on practical reasons (e.g. the walking route project with which we collaborated started in one of the neighbourhoods; which became the physical environmental condition). Measurements will take place at baseline and 3 and 6 months after implementation of the environmental changes.

G*Power was used to perform a sample size calculation [49]. Because the aim of the intervention was to increase walking, our sample size calculations was based on the differences in the change in minutes walked, We used a repeated measures ANOVA design for this purpose, with four groups measured three times. We assumed a small effect size (f) of 0.1. In repeated measures, the correlation between the repeated measurements is also of importance, which we assumed to be 0.5, based on the reliability of the IPAQ (the instrument which was used to measure walking) [50]. Considering a power of 0.8 and a *p*-value of 0.05, a total sample size of 328 older adults is needed [49].

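### Walk-along interviews at T1, held only in the route neighbourhoods, give some likely survey participants study-made exposure to the route before the T2 outcome and awareness measurements

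*Protocol article*

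**What the plan says.** All references are to the protocol article.

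- **Who and what.** Under *Understanding the intervention effect: process evaluation*: "walk-along interviews will be held with 30 participants from neighbourhoods in the physical environment condition". During the interview "the participants walk a part of the walking route with members of the research team". The walk is voice-recorded and GPS-logged, and photographs are taken of notable features.
- **When.** Table 1 (*Measurements*) has "Walk along interviews" in the T1 column only (August/September). T2 is November/December.
- **What follows.** Self-reported walking is measured at T0, T1 and T2, and "The primary outcome measure will be weekly minutes spend walking in leisure time and for transport". The process evaluation section adds: "In the final questionnaire at T2, items about awareness, use and appreciation of the environmental changes". Table 1 also repeats the perceived-environment and Theory of Planned Behaviour measures at T2.
- **Arms.** "These four arms correspond to four neighbourhoods" (*Evaluation design, participants and recruitment*). Two of the four have a route: the physical arm and the combined arm. No accompanied walk is described for the other two.
- **Meaning of participants.** Under *Measurements*, "participants receive a questionnaire pack at each time point", so the word there denotes the survey cohort.

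**The concern.** A researcher-accompanied walk along the route, with conversation about it, makes the interviewee aware of the route and familiar with it. The article's own conceptual framework has the environment act through perceptions and motivation, so the interview touches the mediators under study. The focus groups also reported that walking in company eases safety worries. In the physical-only arm the interview therefore adds a small dose of accompanied walking, which is what the social intervention supplies.

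This contact exists only because of the evaluation, occurs only in the route arms, and precedes T2. Comparison with the control neighbourhood cannot remove it. At stake are the T2 estimates of how many residents noticed and used the route and, to a lesser degree, the T2 contrast in walking.

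**Working it through.** **The plan's own figure.** The article gives a total of 328. Its stated inputs (four groups, three measurements, f = 0.1, correlation 0.5, power 0.8, alpha 0.05), put into the usual group-by-time interaction formula with λ = f²·N·m/(1 − ρ), give 232 rather than 328. A two-group, three-measurement calculation gives 164, or 82 per arm, and 4 × 82 = 328. That mismatch is a separate matter. Here 328 serves only as a denominator, and a second denominator comes from the expected response.

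**Step 1: size of the two route arms.**
- Required sample: 328/4 = 82 per arm, so 2 × 82 = 164.
- Expected response of 15 to 17% of 700: 105 to 119 per arm, so 210 to 238 before attrition.

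**Step 2: share exposed before T2.** Share = 30 / (total in the two route arms). In the social and control arms it is 0.

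**Step 3: shift in the pooled route-arm mean at T2.** Shift = share × x, where x is the lasting change in an interviewee's walking. The documents give no value for x. I assume 0.1 to 0.5 SD; the upper end is high for one partial walk.

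| Route-arm total | Share | Shift at x = 0.1 SD | Shift at x = 0.5 SD |
|---|---|---|---|
| 238 | 12.6% | 0.013 SD | 0.063 SD |
| 210 | 14.3% | 0.014 SD | 0.071 SD |
| 164 | 18.3% | 0.018 SD | 0.091 SD |

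For scale, f = 0.1 corresponds to 2 × 0.1 = 0.2 SD between two equal groups. The shift is thus between about 6% (0.013/0.2) and 46% (0.091/0.2) of the planned effect.

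**Step 4: route awareness at T2.** If all interviewees then report awareness, and true awareness p would otherwise be the same among them as among other residents, the inflation is share × (1 − p). With p assumed to be 20 to 60%:
- lowest: 0.126 × 0.40 = 0.050, about 5 percentage points;
- highest: 0.183 × 0.80 = 0.146, about 15 percentage points.

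**Step 5: after the fix.** If the 30 come from outside the cohort, or are interviewed after returning the T2 questionnaire, the share exposed before the T2 measurements is 0 in every arm.

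**The case against.** The strongest objection is that cohort membership is inferred. The article says that the accelerometer and GPS subsample came from survey responders, but says nothing equivalent about the 30 interviewees. It also uses the word participants for focus-group members and walking-group recruits. If the 30 are other residents, the problem disappears. This stands as a condition on the point, although the *Measurements* section makes cohort membership the natural reading.

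The second objection is size. The contact appears to be one walk along part of the route, about two to four months before T2, in neighbourhoods that already had media coverage, an opening event and a door-to-door route guide and map. At 0.1 SD per interviewee the shift in walking is negligible. This also stands, and it is why the effect on walking can only be called possible and modest. It weakens the awareness argument less: the promotion may have missed an individual resident, but the interview cannot.

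Three stronger readings are tempting but not supported:
- A reader might infer that all 30 come from the physical-only neighbourhood, which would double the share there. The text speaks of neighbourhoods in the plural, and two arms have a route.
- A reader might infer that the interview walk is itself counted as walking in the questionnaire. That could affect T1 only, and only if the walk precedes the T1 questionnaire and falls within its recall period. The order is not given.
- A reader might extend the point to the phone interviews. Table 1 places them at T2, and the text introduces them as following up the final questionnaire, so no defect is shown.

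**Conclusion.** The point holds, on the condition that the interviewees belong to the survey cohort. Followed as written, the plan gives about 13 to 18% of the two route arms a study-made exposure to the route before T2, and gives the other arms none. The T2 awareness and use items are the most directly affected: awareness could be overstated by roughly 5 to 15 percentage points under the assumptions in step 4. T2 walking may move upward in the route arms by 0.013 to 0.091 SD for an assumed 0.1 to 0.5 SD per interviewee; the lower part of that range is the more plausible. The documents contain no evidence on the effect of a single walk-along, so an established upward bias in walking cannot be claimed. The shares would be larger if fewer than 82 per route arm remain at T2. The point should be dealt with because the contamination is specific to the route arms and cheap to avoid, not because it is shown to be large.

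**What to change.** Choose one of two arrangements and state it in the protocol:

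1. Recruit the 30 from residents of the route neighbourhoods who are outside the survey cohort. The cost is a separate recruitment source and no linked survey data for interviewees.
2. Hold each walk-along only after that person has returned the T2 questionnaire, and move the entry in Table 1 accordingly. The cost is outdoor walks in November/December or later with residents aged 55 and above.

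If interviews have already taken place with cohort members, flag these participants and leave them out of the T2 awareness and use estimates. Repeat the T2 walking analysis without them as a sensitivity analysis only. It should not replace the main analysis, because interviewees may be keener walkers and are removed from the route arms alone, which could create a bias in the other direction. Little precision is lost: 328 − 30 = 298 remain, and the four-group interaction formula still gives power of about 0.90 (equal arms assumed, which is approximate after a removal from two arms).

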## Discussion

In this paper we described the development and evaluation protocol of physical and social environmental interventions to promote walking behaviour among older adults living in deprived neighbourhoods. It shows that developing, implementing and evaluating such environmental interventions is challenging, given specific circumstances in the local context in which these interventions were implemented (i.e. specific wishes from the target group, and ongoing activities of other stakeholders).

First of all, the theory and evidence base for developing interventions that modify the physical environment in order to promote physical activity is small. While some socio-ecological frameworks are available, only some of them explicitly inform which environmental factors specifically impact upon physical activity, and what the underlying mechanisms are. Calls have been made to come up with a better understanding of how, when and for whom environmental interventions work [54]. We acknowledge that such understanding is not yet as elaborate as seen in the field of health psychology [57, 67].

A second challenge is that the interventions described in this paper are implemented in ‘the real’ world, which is out of control of the researcher [68]. This means, for instance, that other initiatives may be ongoing with similar goals as the interventions to be developed. In this project, cooperation with various organisations helped us to identify other parties that were already operating (or starting to operate) in the field and strengthen each other’s projects. Therewith we experienced ourselves how important cooperation with local organisations and with different disciplines is. On the other hand, it should be noted that these collaborations also constrain the development and evaluation of interventions for researchers. In our case the decision of the specific route markers in the physical environmental intervention (i.e. painted tiles) was already made, whereas other route markers) could have had advantages over tiles, for instance with regard to visibility. However, ignoring the potential for cooperation would increase the costs, which is undesirable from a cost perspective. An associated challenge is that intervention implementation is out of control of the researcher. Whereas the walking routes were implemented in close collaboration with the project team, by nature, the social environmental interventions were under less control of the research team.

To conclude, we described the development and evaluation of two interventions, one targeting the social neighbourhood environment and the other targeting the physical neighbourhood environment. The evaluation study will provide evidence for their separate and combined effects on walking behaviour of residents. Moreover, it will shed light in how changes to the environment may cause changes in walking behaviour.

## Abbreviations

GIS: Geographic information system
GP: General practitioner
GPS: Global positioning system
MVPA: Moderate-to-vigorous physical activity
NEWS: Neighbourhood environment walkability scale
NGO: Non-governmental organisation
PA: Physical activity
PABS: Physical activity buddy system
SEP: Socioeconomic position
